### Outcome measures

All outcome measurements will be performed by the main researcher at baseline, 8 weeks (after intervention), and 12 weeks (follow-up). Demographic information (i.e., sex, age, body mass index) will be measured before the intervention.

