### Randomization

Participants will be randomized using computer-generated block randomization in a 1:1 ratio, followed by a concealed allocation through opening sequentially numbered, opaque and sealed envelopes; a card inside will indicate the group into which the participant will randomly be allocated, i.e., the intervention or the control group. Participants can discontinue the project at any time. However, all efforts will be made to avoid missing data. The specific way to deal with missing data will be determined at a data review meeting before starting statistical analyses.

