Once the participants can contract the appropriate muscles in a correct alignment during the best movement pattern, they should be able to maintain this for a long time. This goal will be addressed in the improvement phase when necessary tissue adaptations occur by increasing the load of exercises [31, 32]. Placing the participants in weight-bearing positions and using some tools such as training balls and Thera-Bands will reinforce their abilities gradually. During this phase, the participants will only focus on the goal of exercises (external focus) [29]. Moreover, because UCS is representative of underlying potential sensorimotor dysfunction, some functional balance exercises will be included [12]. The frequency and intensity of the exercises will increase progressively during the study, provided that participants can demonstrate good-quality movement. In the final phase, i.e., the maintenance phase, the participants will try to maintain the training adaptations [32]. All exercises will be performed under the supervision of a corrective exercise specialist. The participants will not conduct any extra exercises at home. However, they will be asked to avoid sustaining poor posture. More details about the intervention protocol are presented in Appendix 1. The control group will be asked to do their ordinary daily activities and not to participate in any exercise programs. After the study is completed, the control group will undergo the exercise intervention protocol for ethical reasons.

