#### Outcome measures

Upper trapezius activation (measured with surface electromyography) is the primary outcome measure. Secondary outcomes include electromyography measurements of middle and lower trapezius and serratus anterior muscles, scapular dyskinesis, forward head and shoulder angles, thoracic kyphosis angle, and neck flexion pattern.

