##### Scapular dyskinesis

The current recommendation for clinical assessment based on a prior consensus meeting is the use of the dynamic scapular dyskinesis test according to the procedure described by McClure et al. [35]. The position and motion of scapula are characterized by dyskinesis as a “yes” (presence of deviation or dysrhythmia/asymmetry bilaterally) or “no” (no presence). This method has been shown to be reliable among observers and has acceptable clinical utility [35, 36].

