##### Neck flexion pattern test

The participants will lie supine with knees bent. They will then be instructed to lift the head and look at their toes. Normal movement produces a smooth reversal of the normal cervical lordosis, keeping the chin tucked. Abnormal movement is compensated by the tightness of the SCM, producing an early protraction of the chin directly upward at the beginning of the motion [8].

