## Discussion

We propose to evaluate the effectiveness of a randomized controlled trial of a CCEP in a group of men aged 18 to 28 years with UCS in terms of their alignment, selected muscle activation, and relevant movement patterns.

Clinicians believe that it is important to quantify head, shoulder, scapulae, and spinal posture behavior as they influence and are influenced by many biomechanical, motor control, and performance variables [43]. It has been assumed that exercise can correct postural malalignment, but an earlier review found little evidence to support this assumption [17]. Moreover, despite the widespread inclusion of postural correction in exercise interventions, there are limited empirical data to support its effectiveness and little is known about the most effective exercise interventions [24]. As already mentioned, it seems the most important reason is the adherence to the traditional structural approach in the previous studies. We want to conduct a randomized controlled trial based on the comprehensive approach which is adequately powered and utilizes validated outcome measurements of UCS to investigate the effects of the CCEP on both our primary and secondary outcomes. If the CCEP results in changing the alignment, muscle activation, and movement pattern, or all three, we will examine the pathways of change to determine whether changes in the alignment, muscle activation, or movement pattern can account for the change in the UCS symptoms. Furthermore, if we find out that the CCEP can improve a postural malalignment like in UCS, this evidence could enable practitioners to recommend early intervention for UCS to prevent or delay UCS-associated consequences. Therefore, various experts in the field of corrective exercises and physical therapy, equipped with the knowledge on these changes, can identify people with UCS and also adopt appropriate therapeutic strategies to correct it and prevent the occurrence of secondary consequences.

Our study has some limitations including the recruitment of only men 18 to 28 years of age. Therefore, the results of this study will not be generalizable to all people (e.g., women or men aged ≥ 28 years) with UCS. Another limitation is that this study is not a double-blind design since it is not possible, as is the case with most exercise trials.

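### The main researcher measures every outcome, no masking of assessment or data processing is described, and the one remark on blinding does not justify an unmasked assessor

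*Protocol article*

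**What the plan says.** Under Outcome measures the article gives all measurement to one person: "All outcome measurements will be performed by the main researcher at baseline, 8 weeks (after intervention), and 12 weeks (follow-up"). The outcomes concerned are:

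- **Primary.** "Upper trapezius activation (measured with surface electromyography) is the primary outcome measure". The Electromyography measurements section normalises the signal to MVIC, uses RMS, and sets a numerical rule for onset.
- **Scapular dyskinesis (secondary).** This is an observer's yes/no rating of scapular position and motion.
- **Neck flexion pattern (secondary).** The movement is classed by watching it: "Normal movement produces a smooth reversal of the normal cervical lordosis, keeping the chin tucked", as against early chin protraction.
- **Other secondary outcomes.** These are EMG of three further muscles, head and shoulder angles by photogrammetry, and thoracic kyphosis by flexicurve.

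The Randomization section describes "followed by a concealed allocation through opening sequentially numbered, opaque and sealed envelopes". The Intervention section says "All exercises will be performed under the supervision of a corrective exercise specialist". The only sentence on blinding is a limitation in the Discussion: "Another limitation is that this study is not a double-blind design since it is not possible, as is the case with most exercise trials".

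**The concern.** The stated reason for not being double-blind is sound for men who either exercise under supervision or do not, and for the specialist who supervises them. It gives no reason why the person who rates a scapula or processes an EMG file should know the group. A reader of the article cannot tell whether that person knows it.

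This matters most for the two observer-rated outcomes. Under the eligibility criteria, participants are recruited because the dyskinesis test is abnormal. After baseline, the only change that rating can show is from present to absent, so any leniency toward the exercise arm counts as benefit. The primary outcome is less exposed but not immune, because handling of the MVIC and of the recording comes between the muscle and the number analysed. A bias of this kind does not shrink as participants are added, and the planned repeated-measures ANOVA and t-tests cannot remove it.

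**Working it through.** The plan gives no figure for assessor bias, so there is nothing to reproduce. The check is a comparison of the sections, followed by an illustration.

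**1. What each statement covers**

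- *Envelopes (Randomization)* conceal the next allocation until it is made. They say nothing about who knows the group afterwards.
- *Double-blinding not possible (Discussion)* covers participants and the supervisor. It does not mention the assessor.
- *Main researcher measures everything (Outcome measures)* says who measures, not what that person knows.
- *Corrective exercise specialist supervises (Intervention)* names a second role. It does not say whether this is a different person from the main researcher.

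Taken together, no statement masks the assessor or the processing, and no statement explains the omission.

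**2. Where knowledge of the group could act**

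- *Observer-rated:* dyskinesis and neck flexion pattern.
- *Live measurement:* electrode placement, conduct of the MVIC, and flexicurve tracing.
- *Reading of stored records:* RMS and onset from EMG files, and angles from photographs. The onset threshold is fixed at two standard deviations above rest, in the concentric phase and relative to deltoid onset, so discretion there is narrow.

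Only the third group can be masked afterwards by coding files.

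**3. Illustration of size (the shifts are assumptions, not from the documents)**

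Suppose there is no true effect, and assessment moves the group difference by b SD. The analysis is a two-sided independent t-test at 0.05 with n per arm. Then df = 2n − 2, the non-centrality is b × √(n/2), and the false-positive rate is the probability that the non-central t exceeds the critical value in either direction. The Sample size section gives a minimum of 18 (n = 9) and a target of 24 (n = 12).

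| Assumed b | n = 9: non-centrality | n = 9: false-positive rate | n = 12: non-centrality | n = 12: false-positive rate |
|---|---|---|---|---|
| 0 | 0 | 5.0% | 0 | 5.0% |
| 0.2 | 0.2 × √4.5 = 0.42 | 6.8% | 0.2 × √6 = 0.49 | 7.6% |
| 0.4 | 0.4 × √4.5 = 0.85 | 12.6% | 0.4 × √6 = 0.98 | 15.5% |
| 0.6 | 0.6 × √4.5 = 1.27 | 22.4% | 0.6 × √6 = 1.47 | 29.0% |

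For a fixed shift the error is larger at 12 per arm than at 9, so recruiting more participants is no protection.

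**4. A live step that file coding cannot reach**

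If the MVIC were 10% higher in one arm because of how it was elicited (assumed), the normalised EMG there would fall by 1 − 1/1.10 = 9.1%. The Sample size section treats a 10% difference in muscle activity as clinically meaningful, without saying whether that is relative or absolute. This shows only that MVIC conduct can matter. Nothing in the documents suggests that it will differ by arm.

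**The case against.** The strongest reply is that this is a condensed article, and silence about assessor masking is not proof that there is none. That stands. A reader might infer that the assessor is definitely unmasked, but a trial that is not double-blind can still have a masked assessor, and the article does not say what the main researcher knows. The point survives because the article does address blinding and does assign all measurement to one named role, yet its one explanation does not reach that role.

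Three other inferences also go too far:

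- *That the article declares all blinding impossible.* It says this only of double-blinding, which is fair for supervised exercise against ordinary activity.
- *That full assessor masking is feasible with the present staff.* Only two roles are named, and nothing shows they are two people. If they are one, the assessor necessarily knows who exercised.
- *That the primary outcome is a matter of rater judgement.* It is instrumented. The onset threshold and movement phases are fixed, electrode location follows a published protocol, and Appendix 2 sets the MVIC positions.

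It is also fair to object that coding is imperfect. Someone who has met about 24 participants may recognise them in photographs, and live steps are untouched. This limits what the fix can achieve. It matters little for EMG files, which do not show a face.

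**Conclusion.** The concern holds in a limited form. All outcomes, two of them observer-rated, are measured by the main researcher at every visit. No masking of assessment or processing is described, and the stated limitation does not justify an unmasked assessor.

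The size of any bias is unknown. At an assumed 0.2 SD the false-positive rate would be 6.8% (9 per arm) to 7.6% (12 per arm) instead of 5%, and larger assumed shifts do more harm. These figures rest on the assumed shift, no true effect, and a simple two-group t-test. They do not show that the primary result will be biased or invalid. The case for change is that part of the exposure can be removed at little cost while recruitment is open.

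**What to change.** 1. Export EMG recordings and head and shoulder photographs under random codes, with group and visit removed, before RMS, onset and angles are computed. Someone other than the person processing the files holds the code list. Each session's MVIC, deltoid and test recordings should share one code, so that normalisation and onset can still be computed.
2. Apply the same procedure to stored files from the ten participants reported as enrolled under Trial status.
3. State whether the main researcher and the exercise supervisor are the same person.
   - If they are different, do not tell the main researcher the allocation, and ask participants not to disclose it.
   - If they are the same, state that the live measurements (electrode placement, MVIC, flexicurve, the two movement tests) are unmasked, and interpret the two observer-rated outcomes with that in mind.
4. Reword the limitation in the Discussion to say that participants and the exercise supervisor cannot be blinded, and state separately whether the assessor is masked.

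The cost is a code list and some file handling. Some accidental unmasking will occur, and participants may be recognised in photographs. Coding does not protect the live measurements, and dyskinesis or neck flexion ratings already made cannot be redone from EMG files or photographs.

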#### Outcome measures

Upper trapezius activation (measured with surface electromyography) is the primary outcome measure. Secondary outcomes include electromyography measurements of middle and lower trapezius and serratus anterior muscles, scapular dyskinesis, forward head and shoulder angles, thoracic kyphosis angle, and neck flexion pattern.

##### Electromyography measurements

Surface electromyography of the scapular stabilizer muscles (including upper, middle, lower trapezius, and serratus anterior) will be performed using an ME-6000 Megawin. The participants will execute humeral abduction without resistance in three phases (concentric, isometric, and eccentric) lasting for 3 s each. They will already have been trained to move correctly and at the right speed so that they can perform the movement five times; rest time is 3 s between movements. Disposable Ag-AgCl electrodes with a diameter of 2 cm and a 2 cm spacing between two poles of electrodes will be used and data will be recorded at a frequency of 1000 Hz. The location of the electrodes will be determined using the SENIAM protocol and based on valid scientific papers [33, 34]. The maximum voluntary isometric contraction (MVIC) will be recorded to normalize the signals. More details about the location of the electrodes and MVIC positions are presented in Appendix 2. The data from the mean square root (RMS) will be used in the process of measuring muscle activation. To determine the onset of muscle activity, only the concentric phase of the motion will be used and it will be based on the onset of the deltoid muscle. Moreover, the onset of the activity will be from the point where the level of muscle activity reaches two standard deviations above the rest of the muscle activity [34].

##### Scapular dyskinesis

The current recommendation for clinical assessment based on a prior consensus meeting is the use of the dynamic scapular dyskinesis test according to the procedure described by McClure et al. [35]. The position and motion of scapula are characterized by dyskinesis as a “yes” (presence of deviation or dysrhythmia/asymmetry bilaterally) or “no” (no presence). This method has been shown to be reliable among observers and has acceptable clinical utility [35, 36].

##### Forward head and shoulder angles

The angle of the head and the shoulder will be measured using photogrammetry according to the procedure described by Seidi et al. [15]. The validity and reliability of this method have been established in previous studies [37, 38].

##### Thoracic kyphosis angle

To measure the static alignment of the thoracic spine, the flexicurve method will be used, which is a well-established, valid, and reliable technique [39, 40]. A detailed description of the procedure can be found in previous studies [15, 23].

##### Neck flexion pattern test

The participants will lie supine with knees bent. They will then be instructed to lift the head and look at their toes. Normal movement produces a smooth reversal of the normal cervical lordosis, keeping the chin tucked. Abnormal movement is compensated by the tightness of the SCM, producing an early protraction of the chin directly upward at the beginning of the motion [8].

### Sample size

The sample size was calculated using the G*Power software (G*Power, version 3.0.10, Germany). It was based on a pilot test of seven participants, and on the assumption that a 10% difference in muscle activity [34] and an 11° difference in kyphosis angle [41] between groups would constitute clinically meaningful differences. It was calculated that a sample consisting of at least 18 participants would suffice to obtain 80% power with d = 0.80 effect size, and a confidence interval of 0.95. It should be noted that the effect size was reported in the previous study which compared scapular muscle activity between the interventions and control groups. Effect sizes ranged from 0.6 to 0.9 for the EMG amplitude and onset [42]. Since a few participants may drop out of the intervention studies, we will include 24 (assuming a drop-out rate of approximately 25%).

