### Statistical method and analysis

Assessments of statistical procedures will be performed using IBM SPSS version 20 for Windows (SPSS Inc., Chicago, IL, USA). All variables will be reported using the descriptive statistic (mean, standard deviation). Shapiro-Wilk test will be used to assess the normality of data. Repeated measures ANOVA will be used to compare the means. If mean difference is significant, then the Bonferroni-adjusted post-hoc test will be calculated. The independent *t*-test will also be used for comparison between groups. Finally, the effect size will be calculated for the magnitude of the difference using the Cohen method. The significance level will be set at *p* < 0.05.

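### The stated 80% power with 18 participants at d = 0.80 does not follow from the inputs given; the named between-group t-test has about 36%

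*Protocol article*

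**What the plan says.** The Sample size section of the protocol article reports a G*Power calculation in which "a sample consisting of at least 18 participants would suffice to obtain 80% power", "with d = 0.80 effect size, and a confidence interval of 0.95". The effect size is taken from a study that "compared scapular muscle activity between the interventions and control groups", where "Effect sizes ranged from 0.6 to 0.9 for the EMG amplitude and onset". The 18 is then raised to 24 to allow for roughly 25% drop-out.

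Under Randomization: "Participants will be randomized using computer-generated block randomization in a 1:1 ratio". Statistical method and analysis names repeated measures ANOVA first, and then an independent t-test that "will also be used for comparison between groups". It adds: "The significance level will be set at *p* < 0.05". The Discussion describes a trial "which is adequately powered and utilizes validated outcome measurements of UCS".

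The article does not state the G*Power test family, the sidedness of the test or a within-person correlation.

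**The concern.** A standardised between-group difference of 0.80 usually needs about 25 people per arm for 80% power. Nine per arm is about a third of that. The enrolment target of 24 and the Discussion's adequacy claim both rest on the figure of 18, and the article offers no other justification of size. If the real power is well below 80%, a non-significant primary result says much less than the article implies, and a significant estimate will tend to exaggerate the effect.

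**Working it through.** **Inputs from the article.** d = 0.80, between groups (Sample size). Alpha 0.05 (Statistical method and analysis); two-sided is assumed, with one-sided also shown. Allocation is 1:1 (Randomization). The total is 18, because 18 / (1 − 0.25) = 24, which is the enrolment target. So n = 9 per arm, and the drop-out step itself is correct.

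**Independent t-test.** With n per arm, the noncentrality is δ = d·√(n/2) on 2n − 2 degrees of freedom.

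- n = 9: δ = 0.80 × √4.5 = 1.697, df = 16, two-sided critical value 2.120. Power is 35.8%. One-sided (critical value 1.746), it is 49.2%.
- n = 12 (all 24 complete): δ = 0.80 × √6 = 1.960, df = 22, critical value 2.074. Power is 46.6%.
- n = 9 over the article's quoted range of effects, two-sided: 22% at d = 0.6 and 43% at d = 0.9.

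The stated 80% is not reproduced. Solving for n at d = 0.80, 25 per arm gives 79.1% and 26 per arm gives 80.7%, so 26 per arm (52 in total) are needed. One-sided, the answer is 21 per arm (42 in total). Solving for d at 80% power gives 1.41 with 9 per arm and 1.20 with 12 per arm. Reading 18 as the number per arm gives 64.5% two-sided and 76.0% one-sided, and would not fit the step to 24.

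**Repeated measures ANOVA, group-by-time test over three visits.** Assumptions: equal group means at baseline, a difference of d = 0.80 at both week 8 and week 12, and the same correlation ρ between every pair of visits. The group differences are (0, d, d), with mean 2d/3. Half the deviations from that mean are −d/3, d/6 and d/6, so

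f² = (d²/9 + d²/36 + d²/36) / 3 = d²/18, and f = 0.80/√18 = 0.189.

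The noncentrality is λ = f²·N·3/(1 − ρ), on 2 and 2(N − 2) degrees of freedom. For N = 18, λ = 1.92/(1 − ρ). For N = 24, λ = 2.56/(1 − ρ).

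| ρ (assumed) | λ, N = 18 | Power, N = 18 | λ, N = 24 | Power, N = 24 |
|---|---|---|---|---|
| 0.5 | 3.84 | 36.9% | 5.12 | 48.5% |
| 0.7 | 6.40 | 57.1% | 8.53 | 71.6% |
| 0.8 | 9.60 | 75.7% | 12.80 | 88.2% |

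Power reaches 80% at ρ of about 0.82 with 18 participants and about 0.75 with 24.

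**Can the software return 18?** Yes, under some settings of the interaction option:

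- f = 0.40, three visits, ρ = 0.2: 80.8% at N = 18 (75.1% at 16).
- f = 0.40, two visits, ρ = 0.4: 82.8% at N = 18 (77.5% at 16).
- f = 0.25, three visits, ρ = 0.7: 82.5% at N = 18.

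None of these is d = 0.80. With two visits f = d/4, so f = 0.40 means a difference in change of 1.6 SD. With three visits and the pattern above d = f·√18, so f = 0.25 means d of about 1.06 and f = 0.40 means about 1.70.

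**The case against.** The strongest reply is that the t-test is the less efficient of two planned analyses. Repeated measures ANOVA is named first, the t-test is an addition, and the test behind the 18 is not identified. The seven-person pilot could have supplied a high correlation that a condensed article left out. With ρ of about 0.82 the group-by-time test does reach 80% with 18 participants, and if all 24 complete it needs only about 0.75.

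This part stands, and it limits the conclusion. A reader might infer that the adequacy claim is proven false. The documents do not support that, because a high enough correlation would make it true for the repeated measures test. A reader might also infer that the trial would miss a true effect of d = 0.80 about two times in three. That holds only for the two-sided t-test with 18 completers; with 24 completers the same test misses it 53% of the time, and the repeated measures test less often if the correlation is high. Nor can one say that no standard calculation gives 18, since the settings above do.

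The reply does not rescue the printed statement. It gives a between-group d and no correlation, and from those inputs 80% does not follow. The favourable repeated measures figures also assume that the full effect persists through the 4 weeks of detraining.

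**Conclusion.** The power statement is wrong as written: d = 0.80, 18 participants in total, 1:1 allocation and alpha 0.05 do not give 80% power for a between-group comparison. The shortfall is large. The named t-test has 36% power instead of 80%, and needs 52 completers instead of 18. For the repeated measures test, power with 18 participants lies between about 37% and 76% for assumed correlations of 0.5 to 0.8. The t-test figures rest only on the article's inputs and a two-sided test. The repeated measures figures rest also on the assumed correlation, equal baselines and an equal effect at both later visits. The adequacy claim in the Discussion is unsupported by the stated inputs, which is weaker than disproved.

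**What to change.** Leave recruitment as it is and replace the power sentence in Sample size with wording such as:

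> With 18 evaluable participants (9 per arm), a two-sided 5% independent t-test has about 36% power for d = 0.80 and 80% power for d of about 1.4. The repeated measures group-by-time test has about 37% to 76% power for d = 0.80 at both later visits, at assumed within-person correlations of 0.5 to 0.8.

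In the Discussion, remove the adequacy claim or qualify it with these figures. If the sponsor holds a correlation from the pilot, state it together with the test and sidedness that produced 18, and give the power at that value.

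The cost is that the stated power becomes less favourable. No further participants and no change to the analysis are required.
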